### Setting and participants

The trial plans to recruit participants within three National Healthcare Service Trusts in northern and southern England, covering four individual neonatal units (three tertiary level intensive care units and one local neonatal unit). All sites have at least one dedicated infant feeding support professional and counselling or psychological support is available. All sites have hospital-grade pumps available for use in the hospital and a loan scheme for free use at home. Breastmilk feeding rates at discharge are variable, with one site below the regional and national averages and the others above average [42]. Two Trusts have level 3 Unicef Baby Friendly Initiative accreditation and one has not yet started the accreditation process. All sites are urban and serve a range of communities, including diversity of ethnic origin and social deprivation.

Participants are mothers of infants born between 23^+0^ and 31^+6^ weeks of gestation. Full inclusion and exclusion criteria are provided in Fig. 1. Participants with more than two live born infants are excluded and participants must have an intention to express milk for at least 2 weeks after birth to join the trial. Participants can be screened by research nurses and trained clinicians during pregnancy and after birth. Participants must provide written, informed consent (either on paper or electronically) and are provided with written information sheets. Randomisation can only take place between birth and midnight on day 3 after birth.

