### Primary outcome

The primary outcome is defined as the highest 24-h expressed milk weight recorded on any of day 4, day 14 or day 21 (E1, E2 or E3; in grams). If the participant declares that they are no longer expressing, the milk weight for that day is accorded a value of zero. Table 3 shows various scenarios of what this means in practice. The reason for this definition of the primary outcome, instead of using 24-h expressed milk weight at a specific timepoint such as day 21, is that some more mature infants may start to directly breastfeed by day 21 and this is likely to decrease expressed milk yield. In addition, some parents may choose to stop expressing before day 21 but increasing their milk yield prior to this would still be an important outcome to reduce infant morbidity. Finally, the physiology of lactation studied in term infants [46] suggests that once a milk supply is established, it is robust to supply and demand—therefore, achieving a higher milk yield at day 14 than day 21 suggests that the parent will be able to increase their yield as needed with more frequent expressing in the future.

**Table 3 Tab3:** Examples of primary outcome calculation

	Day 4	Day 14	Day 21	Primary outcome
**Scenario 1**	300g	500g	750g	750g
**Scenario 2**	100g	450g	400g	450g
**Scenario 3**	50g	missing	missing	50g
**Scenario 4**	50g	150g	Stopped expressing (0g)	150g

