### Statistics and analysis

#### Sample size and power calculation

In the most relevant previous study [25], mean expressed milk yield at day 14 of the trial increased from 318 ml (standard deviation; SD 309 ml) to 862 ml (SD 309 ml) with the use of a visualisation/relaxation soundtrack. Initial exploratory work suggested that baseline milk yield in the recruiting sites is higher than this, and therefore, this study is powered to detect an increase in highest 24-h expressed milk yield from 670g (SD 300g) to 825g (SD 300g), with 80% power and a two-sided significance level of 0.05. This is a 155g absolute mean difference or a 0.5 standardised mean difference. In total, 118 participants are required, so the recruitment target was set at 132 to allow for 10% attrition. Since breastmilk has an average specific gravity of 1.03 [62, 63], 670g is estimated as equivalent to 650ml and 825g is estimated as equivalent to 800ml, although much of the literature views volume and mass measurements as interchangeable for breastmilk [64–66].

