#### Description of statistical methods

Demographic and clinical data will be summarised with counts and percentages for categorical variables, means (with SDs) for normally distributed continuous variables and medians (with interquartile or simple ranges) for other continuous variables.

Statistical analysis of continuous outcomes will use linear regression with adjusted and unadjusted mean differences presented, or quantile regression with median differences presented, as appropriate. Binary outcomes will be analysed using log binomial regression, or Poisson regression with a robust variance estimator if the model fails to converge, and risk ratios will be presented. 95% confidence intervals will be presented.

Analyses will be adjusted for the stratification factors (recruiting neonatal unit, gestational age at birth and whether the participant has one or two babies alive at randomisation) where possible. The STAI score at day 21 will be adjusted for the STAI score at baseline. The primary outcome will be adjusted for the associated measurement day of the highest milk weight. Both crude and adjusted estimates will be presented, but the primary inference will be based on the adjusted estimates. Further process indicators, such as number of direct breastfeeds, will be summarised by randomised arm, with no comparative statistics presented.

Participants will be analysed in the groups to which they were randomly assigned, comparing the outcome of all participants allocated to intervention with all those allocated to the comparator group, regardless of deviation from the protocol or treatment received (the Intention to Treat population). Analysis will take place on a superiority basis.

Exploratory subgroup analysis will use a statistical test of interaction to examine the effect of the intervention on the primary outcome by gestational age at birth (<28 weeks and ≥ 28 weeks). Stratified analysis by the other stratification factors described and exclusive breastmilk feeding intention at baseline will take place with no formal test for interaction. This is to limit multiple comparisons and due to the low statistical power for subgroup analysis.

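### The primary model adjusts for the day of the highest yield, a post-randomisation variable taken from the outcome itself, so the primary estimate can lose part of the true effect

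*Protocol article*

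**What the plan says.** All references are to the protocol article.

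- **Outcome** (Primary outcome): "The primary outcome is defined as the highest 24-h expressed milk weight recorded on any of day 4, day 14 or day 21". On stopping: "If the participant declares that they are no longer expressing, the milk weight for that day is accorded a value of zero". In Table 3, Scenario 3, a mother whose day 14 and day 21 logs are missing is scored on day 4 alone.
- **Timing** (Setting and participants): "Randomisation can only take place between birth and midnight on day 3 after birth". All three measurement days come later.
- **Model** (Description of statistical methods): "The primary outcome will be adjusted for the associated measurement day of the highest milk weight". The stratification factors are also included. No reason is given for the day covariate.
- **Inference** (same section): "Both crude and adjusted estimates will be presented, but the primary inference will be based on the adjusted estimates". The section also commits to comparing everyone as randomised.
- **Sensitivity analyses** (same section): day 21 yield only, and separately leaving out day 4 logs. Multiple imputation and/or a pattern mixture model is planned if more than 10% of primary outcome data is missing.

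**The concern.** The covariate is the position of the maximum among the same yields whose maximum is the outcome. It is not a baseline characteristic, and the intervention can change it. A mother who stops early has day 4 as her best day; one who sustains or builds her supply has day 14 or 21.

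The protocol itself expects such a pathway. The Background proposes that less-stressed mothers may adopt a more effective expressing regime. The Primary outcome section notes that "some parents may choose to stop expressing before day 21 but increasing their milk yield prior to this would still be an important outcome". If the recording acts in this way, it moves mothers from an early to a later best day. Comparing the arms within best day then takes that movement out of the estimate.

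The covariate also merges two different situations. A mother with 50 g on day 4 who then stopped, and a mother with 50 g on day 4 whose later logs are missing, both have day 4 as best day. The first is an outcome and the second is a gap in the data.

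At stake is the meaning of the primary estimate. It would be conditional on a possible consequence of treatment, although the plan promises an intention-to-treat comparison.

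**Working it through.** **1. The plan's own sample size.** Inputs from Sample size and power calculation: difference 825 − 670 = 155 g, SD 300 g, "with 80% power and a two-sided significance level of 0.05".

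n per arm = 2 × (1.960 + 0.842)² × 300² / 155² = 58.8, so 59 per arm and 118 in total. With 10% attrition, 118 / 0.90 = 131.1, so 132. Both figures reproduce. This is an unadjusted comparison of two means with no day covariate.

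**2. Why the covariate removes effect.** Let p be the share of an arm with a given best day, and m the mean highest yield among those mothers. The crude difference is the sum over days of p·m (intervention) minus p·m (control). It has two parts: differences in m within a day, and differences in p between arms. A model with day indicators keeps roughly the first part and drops the second.

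Illustration with assumed values: best day 4/14/21 in 15/30/55% of controls and 5/30/65% of the intervention arm, with means 200/600/760 g in both arms.
- Control: 0.15 × 200 + 0.30 × 600 + 0.55 × 760 = 628 g
- Intervention: 0.05 × 200 + 0.30 × 600 + 0.65 × 760 = 684 g
- Difference: 56 g, which is 56 / 155 = 36% of the target and lies wholly in the second part.

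**3. Range over effect patterns.** Simulation with 400,000 mothers per pattern. The maximum was regressed on arm, without and with day indicators. Assumed control means are 150/580/600 g, SDs 120/270/300 g and correlations 0.35 to 0.8. These give a control maximum of about 666 g (SD 273 g), near the planned 670 g (SD 300 g).

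| Assumed effect on day 4/14/21 | Without day (g) | With day (g) | Lost |
|---|---|---|---|
| None | −0.6 | −0.6 | – |
| Equal, 150 g each day | 149.0 | 148.4 | 0.4% |
| Proportional, 23% | 133.6 | 124.6 | 6.7% |
| Growing, 20/110/170 g | 145.8 | 126.1 | 13.5% |
| Day 21 only, 250 g | 191.4 | 142.2 | 25.7% |
| Peak at day 14, 60/170/100 g | 136.7 | 138.9 | −1.6% (a rise) |
| Fewer mothers stopping, no other effect | 84.7 | 4.2 | 95.0% |

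In the last row, 20% of controls and 5% of the intervention arm stop before day 14, and a further 15% and 5% before day 21. Its control maximum is 552 g (SD 318 g), so it fits the planning values less well.

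**4. Power.** With 59 per arm and SD held at 300 g, the standard error is 300 × √(2/59) = 55.2 g. Power is 80% at 155 g, 71% at 139.5 g (10% lost), 61% at 124 g (20% lost) and 50% at 108.5 g (30% lost). This ignores the precision that the covariate adds. A separate simulation at 59 per arm, with the same control means, includes it:
- equal effect on all days: power 76% without the covariate, 88% with it;
- growing effect: estimate 120 g falls to 105 g, yet power rises from 53% to 60%;
- stopping cut from 15% to 5% plus a yield gain: 142 g falls to 82 g, and power from 72% to 40%.

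**5. Stopping versus missing logs.** With the assumed day 4 mean of 150 g and a maximum of 666 g, a 10-point difference between arms in mothers scored on day 4 alone is worth 0.10 × (666 − 150) = 52 g.
- Stopping cut from 15% to 5% (a real benefit): simulated 51 g crude, about −1 g day-adjusted.
- Later logs missing in 15% versus 5%, with no true effect (an artefact): simulated crude bias about +51 g, day-adjusted about −1 g.

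The covariate removes both alike.

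**The case against.** **Other planned analyses would show the problem.** The crude estimate is reported. In the day-21-only analysis the covariate is constant and drops out, and mothers who have declared that they stopped count as 0 g. This stands as a means of detection. A reader might infer that a real benefit through sustained expressing would simply be reported as null; the documents do not support that, because both analyses would show it. Neither carries the primary inference, however. The crude estimate also omits the stratification factors. Day 21 yield alone is the measure the plan rejected as primary, because direct breastfeeding may lower it.

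**The size is unknown.** This stands in full. The protocol gives no yields by day and no stopping rates, and mothers enter only if they intend to express for at least 2 weeks, so heavy early stopping is not a given. The near-total loss applies to one pattern only, and the estimate can rise slightly if the effect peaks at day 14.

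**The covariate may guard against unequal missing logs.** This stands in part. Participant remuneration reports higher than expected loss to follow-up for the primary outcome, and step 5 shows the covariate offsetting the resulting bias. That purpose is inferred, since the protocol states none. The guard also works by discarding a genuine effect on stopping, so it cannot replace proper handling of missing data. Deleting the covariate and doing nothing else would still give up some protection.

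**Conclusion.** The point holds. The primary inference rests on a model conditioned on a post-randomisation variable derived from the outcome, contrary to the stated intention-to-treat comparison and to the unadjusted 155 g on which the sample size is based. This follows from the text without any assumption.

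The loss does depend on assumptions: none if all days rise equally, roughly 7 to 26% for a proportional, growing or day-21-only effect, and nearly all if the recording works only through continued expressing. The sponsor cannot know beforehand which applies.

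Two stronger readings should be resisted. A reader might infer a raised false-positive risk. When the recording changes nothing, including the best day, both models are unbiased, and a separate null simulation of 3000 runs rejected about 5.6% of the time under each. A reader might also infer a definite fall in power from the planned 80%. Step 4 shows that power can move either way, because the covariate also adds precision. How to code a mother with 0 g on every day is a detail for the analysis plan and forms no part of this finding.

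**What to change.** Before analysis, amend the protocol and the analysis plan as follows.

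1. Remove the measurement-day covariate from the primary model. Base the primary inference on adjustment for recruiting unit, gestational age group and one or two babies.
2. Keep the day-adjusted model as a sensitivity analysis.
3. Apply the multiple imputation already named in the plan to the day-specific yields, then take the maximum. A missing day 14 or 21 log then counts as missing data and not as a day 4 maximum, while a declared stop stays at 0 g. As Table 3 scores it, Scenario 3 has an observed primary outcome, so a trigger based on missing primary outcomes would not count it.

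The cost is a few sentences, with no new data and no change to 118 or 132. Some precision is lost if the recording does not alter the best day. Adding baseline items on feeding experience and intention could recover part of it, but this is optional.

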## Methods

### Aim and design

This is a multi-centre, unmasked, randomised controlled, parallel-group trial designed to determine if a self-directed relaxation and visualisation intervention for mothers of infants born between 23 weeks of gestation and 31 weeks and 6 days of gestation improves lactation and mental health outcomes. Both groups will receive standard clinical support for lactation provided by their neonatal unit staff. The intervention is a 12-min-long modified audio recording that participants are requested to listen to frequently while expressing breastmilk. The primary objective is outlined in Table 1.

**Table 1 Tab1:** Primary objective in PICO format

	Primary objective
**Population**	Mothers of one or two infants born between 23+0 and 31+6 weeks’ post-menstrual age
**Intervention**	Provision of specific relaxation and visualisation recording with instruction to listen frequently while expressing breastmilk
**Control**	Standard care, including standard lactation support provided by neonatal unit staff
**Outcome**	Expressed milk yield in 24 h (highest value recorded on any of day 4, day 14 or day 21 after birth)

Data is submitted directly by participants into case report forms and through participant responses to short message service (SMS) messages. Research staff enter baseline and secondary outcome data from the participant and infant medical notes. The trial aims to recruit a total of 132 participants. The trial design is summarised in Fig. 1.

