### Randomisation

Participants will be randomised with a 1:1 allocation using stratified permuted block randomisation by a secure web-based randomisation programme hosted by the National Perinatal Epidemiology Unit Clinical Trials Unit. Stratification will be based on recruitment neonatal unit, gestational age at birth (23^+0^ to 27^+6^ weeks versus 28^+0^ to 31^+6^ weeks) and multiple birth (one versus two babies alive at time of randomisation). Research staff and the participant are aware of the allocation after randomisation, as the study is unmasked. Study identification numbers are not consecutive, to reduce the possibility of research staff monitoring the sequence of allocation.

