An exploration of adherence effect on the primary outcome will be conducted, dividing the intervention group into high- and low-frequency adherence by their reported number of times listening to the recording. An exploration of perceived relaxation effect on primary outcome will be conducted, dividing the intervention group into those who report the intervention to be relaxing and those who do not (via Likert scale). Summary statistics will be presented, with no statistical inference.

Basic demographics of the recruited participants will be compared with aggregate data from the potentially eligible population with no statistical inferences made.

Primary analysis will take place on a complete case basis. If more than 10% of primary outcome data is missing, sensitivity analysis will be performed to explore the pattern of missingness for the primary outcome, using multiple imputation and/or a pattern mixture model as appropriate. Sensitivity analyses will also assess whether the definition of the primary outcome has led to bias by assessing the impact of using day 21 expressing yield only, and separately of excluding day 4 logs. Stata will be used for all analysis.

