### Participant remuneration

Each participant will be provided with a small digital weighing scale, a coolbag and a pen. They will be offered a set of headphones if in the intervention group. Due to higher than expected loss to follow-up for the primary outcome, an amendment was approved after recruitment started to provide a £10 electronic food and drink voucher code to participants during the expressing phase. This is an unconditional thank you gift for the participant with the aim to increase the participant’s feeling of connection with and positivity about the trial.

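### The missing-data sensitivity analysis for the primary outcome depends on a single 10% threshold that takes no account of imbalance between arms

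*Protocol article*

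**What the plan says.** All of the analysis rules below are in the protocol article, under Description of statistical methods.

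- Main analysis: "Primary analysis will take place on a complete case basis".
- Condition for the missing-data check: "If more than 10% of primary outcome data is missing, sensitivity analysis will be performed to explore the pattern of missingness".
- Methods once the condition is met: "using multiple imputation and/or a pattern mixture model as appropriate".
- Two further sensitivity analyses carry no condition. They look at the outcome definition by "assessing the impact of using day 21 expressing yield only, and separately of excluding day 4 logs".

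Elsewhere in the article:

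- Randomisation: "Research staff and the participant are aware of the allocation after randomisation, as the study is unmasked". Allocation is 1:1.
- Data collection: mothers weigh their own milk and submit their own logs.
- Measures to improve data quality and retention: only the intervention group gets text reminders on days 9 and 17 to use the recording.
- Primary outcome: the highest of up to three 24-hour weights. Table 3, scenario 3, shows that one log is enough for the outcome to be present. A mother who declares that she has stopped expressing is scored 0 g for that day.
- Withdrawal and change in consent: withdrawals and consent changes are reported by arm, with reasons.
- Participant remuneration: a voucher was added after recruitment began. The reason given is "Due to higher than expected loss to follow-up for the primary outcome".

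**The concern.** A complete-case comparison of means is biased when the fraction missing differs between arms and the missing mothers differ from the observed ones, or when the gap between missing and observed mothers itself differs between arms. A pooled percentage captures neither. Under the stated rule a symmetric 12% loss calls for the check, while a loss of nearly a fifth of one arm and none of the other does not.

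Arm-related non-return is plausible here. Mothers know their allocation, returning a log is their own action, and the intervention group has extra contact shortly before the day 14 and day 21 logs. If low-yield mothers fail to return logs mainly in the intervention arm, the estimate is inflated. If they do so mainly in the control arm, a real benefit is hidden. In either case the primary result could be published without the one analysis that tests it.

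**Working it through.** **Inputs.** From the protocol article: "The trial aims to recruit a total of 132 participants" (Aim and design); 1:1 allocation, so 66 per arm expected (Randomisation); target difference 825 − 670 = 155 g, SD 300 g, 80% power, two-sided 0.05, 118 evaluable, 10% attrition (Sample size and power calculation). Assumed, not in the document: the average shortfall *d* of missing mothers relative to observed mothers, taken as 100, 200 or 300 g and equal in both arms.

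**The plan's own figures.** Per arm, 2 × (1.960 + 0.842)² × 300² / 155² = 58.8, rounded up to 59, so 118 in total. Then 118 / 0.9 = 131.1, and 132 keeps the arms equal. Both stated numbers reproduce.

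**How many can be missing without meeting the condition.** 13/132 = 9.85%, not above 10%. 14/132 = 10.6%, above it. So the most is 13. By arm:

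- 13 v 0: 19.7% v 0%
- 11 v 2: 16.7% v 3.0%
- 9 v 4: 13.6% v 6.1%

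**How unusual these splits are by chance.** If each of the 13 is equally likely to fall in either arm, the two-sided probability of a split at least as uneven is:

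- 13 v 0: 2 × 1/8192 = 0.0002
- 11 v 2: 2 × (78 + 13 + 1)/8192 = 0.02
- 9 v 4: 2 × (715 + 286 + 78 + 13 + 1)/8192 = 0.27

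So 9 v 4 is ordinary. The other two would themselves point to loss related to arm.

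**Bias and type I error.** Bias = (fraction missing in arm A − fraction missing in arm B) × *d*. SE = 300 × √(1/n₁ + 1/n₂) on the numbers analysed. For 13 v 0 this is 300 × √(1/53 + 1/66) = 55.3 g, and it is about 55 g for the other splits. Type I error = P(|N(bias/SE, 1)| > 1.96), unadjusted.

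| Split | d = 100 g | d = 200 g | d = 300 g |
|---|---|---|---|
| 9 v 4 | 8 g, 5.2% | 15 g, 5.9% | 23 g, 7.0% |
| 11 v 2 | 14 g, 5.7% | 27 g, 7.8% | 41 g, 11.5% |
| 13 v 0 | 20 g, 6.5% | 39 g, 11.0% | 59 g, 18.7% |

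Worked example, 13 v 0 with 300 g: 13/66 × 300 = 59.1 g, which is 38% of 155 g; 59.1/55.3 = 1.07; type I error 18.7%. At the mild end, 9 v 4 with 100 g: 5/66 × 100 = 7.6 g, about 5% of 155 g.

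**Whether anything else in the plan covers this.** The day-21-only and day-4-exclusion analyses use observed logs, so a mother with no log is absent from both. The by-arm report covers withdrawal and consent change; it describes losses without testing the estimate, and simple non-return of logs need not appear in it.

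**The case against.** Four points are fair.

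1. **The condition may be met anyway.** The remuneration section reports loss above expectation for the primary outcome itself. That outcome already counts as present with one log, so on a plain reading the reported loss is what remains after that allowance. Planned attrition was 10%, the same as the threshold. This stands and lowers the practical weight. It does not settle the matter, because no figure is given and the voucher was meant to reduce the loss. It would be wrong to read the reported loss as evidence that the check will be skipped; it points the other way.

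2. **One informative group is already handled.** Mothers who declare that they have stopped expressing enter as 0 g. The outcome is missing only when no usable record exists on any of the three days. This stands. Nothing in the document supports a full 1 SD deficit among those who remain missing.

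3. **The largest figures stack extremes.** A reader might infer that the plan lets an arm lose a fifth of its mothers with type I error near 19%. That needs exactly 13 missing, all in one arm, with a 300 g deficit. The document gives no sign of such a pattern, and primary inference uses adjusted estimates, which this arithmetic does not model.

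4. **The rule does not forbid the check below 10%.** A reader might infer that the analysis is switched off; it is only not required. Nor does the text say whether the 10% is overall or per arm. Overall is the plain reading. Even per arm, 6/66 (9.1%) v 0 would pass unchecked.

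It could also be said that this is detail for the analysis plan. The range of shifts is; the threshold is not, because the protocol states it.

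**Conclusion.** The point holds as a bounded weakness in a stated rule. The missing-data sensitivity analysis hangs on a percentage that does not measure what drives bias, so up to 13 of 132 missing, however split, leaves it optional. Under the assumed deficits the consequence runs from negligible (about 8 g, type I error about 5%, at 9 v 4 with 100 g) through moderate (about 41 g, 11.5%, at 11 v 2 with 300 g) to serious only in the extreme case (about 59 g, 19%, at 13 v 0 with 300 g). These sizes rest on the assumed deficit, the assumption that it is the same in both arms, SD 300 g, 66 per arm and an unadjusted normal test. The document does not show that such imbalance occurred. The complete-case primary analysis can stand; its missing-data assumption should be tested regardless of the percentage.

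**What to change.** Under Description of statistical methods, delete the 10% condition. State that missingness of the primary outcome will be reported by arm, counting non-return of logs as well as withdrawal. Run both methods already named, multiple imputation and a pattern-mixture (delta-adjusted) analysis, whatever the percentage missing, with the assumed shift allowed to differ between arms. The range of shifts can be set in the statistical analysis plan before allocation-level outcome data are seen. The cost is one changed sentence and a short extra analysis. No new data are needed, and the sample size and the primary analysis do not change.
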